**Table 2 Tab2:** **Survey constructs and origins**

Primary outcomes	Purported mediators	Other variables
Fruit and vegetable servings [51]	Community of practice scale [52]	Demographics; health, work and habits history
Sugary drinks, fats and snacks [53]	Social support [54]	Job strain [55]
Self-reported physical activity scale [35]	Team cohesion [56]	Work stress [57]
Safety compliance [58]		Sleep deficiency [53, 59]
Self-reported tool use		Interpersonal conflict [60]
		Occupational Fatigue Inventory [61]
		Self-reported injury, workers’ compensation claims
		Bodily pain/musculoskeletal complaints [62, 63]
		Family work conflict [64]
		Family supportive supervisor behaviors [65]
		Positive and negative affect [66]
		Loneliness [67]
		Mood CES-D [68]
		Perceived stress [69]
		Stressful events [70, 71]
		Life satisfaction [72, 73]

The physiological assessment includes height, weight (Tanita scale; Model 310GS, Tanita Corporation of America, Inc., Arlington Heights, Illinois, USA) and blood pressure (OMRON Model HEM-907XL, Omron Healthcare, Inc., Lake Forest, Illinois, USA,). Fasting blood via routine finger sticks and capillary tube are analyzed for blood glucose, cholesterol, and triglyceride concentrations (Cholestech PA Analyzer, Hanson Medical Systems, Inc., Winter Park, Florida, USAA 6-minute walk test is used as an index of fitness [74]. A body mechanics assessment is performed using tasks: 1) picking up a bag of groceries from the trunk of a car, 2) picking up a box from the floor, 3) picking up a pen from the floor, and 4) buttoning the shirt of a client. Task demonstrations are videotaped and still shots identified at participant contact with object. Measurements of participant trunk flexion in degrees are obtained using a goniometer and compared to published risk ranges [75].

The consumer-employers of intervention and control participants also will be surveyed with an instrument that includes demographic questions, observations about safety behaviors and ratings regarding satisfaction with their HCW, using the 13-item Home Care Client Satisfaction Inventory [76]. Study participants deliver sealed survey packets to their consumer-employers that include information and the survey, as well as a pre-paid return addressed envelope.

#### Qualitative

Session observers take notes concerning the problem-solving topics discussed, items mentioned in reflections and other general observations. During the 6- and 12-month health assessments, semi-structured interviews will explore the process of attending sessions and behavior change. Open-ended questions will probe emergent themes, and those interviews are recorded for later transcription and analysis.

### Fidelity and adherence

A research staff member observes each COMPASS session, and the scripted curriculum provides a check list of session components to index fidelity and dose. The observer also takes notes as part of qualitative data collection.

### Power and sample size

Our wave one target sample was planned as 160 subjects (8 groups of 10 participants per condition), which is powered to detect changes in primary health promoting behavioral outcomes at the 6-month time point (0.85 power), based on effect sizes concerning specific eating behaviors (frequency of sugary drink and sugary snack consumption) from another population of lone workers [77] and an estimated intraclass correlation of 0.02 for health behaviors, based on a meta-analysis of intraclass correlations in studies of health behaviors [78]. The design also provides acceptable (but not exceptional) power to detect maintenance effects at the 12-month time point (0.74 power). Based on the original wave's eight intervention and eight control groups, the study should have moderate power (0.72) to detect mediated effects at the 6-month time point where both of the paths to and from the purported mediator exhibit medium effect sizes (that is, a = 0.3 and b = 0.3). The wave two mediational model will be compared with the wave one findings. While power will be limited given the smaller sample size of 40 participants (four groups) in the second translational wave, we will compare effect sizes in each pathway as they relate to the model of mechanisms developed with the original cohort.

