## Methods

### Overview and timeline

The COMPASS trial is a cluster randomized controlled trial. Both intervention and the usual care control condition participants will complete health assessments and surveys prior to the intervention (month 0), at the end of intervention phase 1 (month 6) and at the end of intervention phase 2 (month 12). Additional funding is being sought for longitudinal assessments at 24 months.

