#### Quantitative

The HCW survey includes demographic, work-health history items and a battery of outcome and potential mediating measures. The survey emphasizes constructs with established reliability and validity. Behavioral items, unless otherwise noted, are anchored “in the past month.” Constructs and instruments used are presented in Table 2. The primary outcomes and purported mediators are indicated. Other variables are more distal outcomes, potential moderators of intervention effects or constructs added to align with other intervention trials being conducted at the Oregon Health Workforce Center of Excellence (http://www.cdc.gov/niosh/twh/centers.html).

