For the initial randomized control trial wave, all participant data will be used, and group assignment will be represented by a dummy code variable (that is, intervention = 1, control = 0), using the pretest measures as predictors of the corresponding post-test outcomes and medicating variables, with the dummy code variable accounting for group differences at baseline. Once that mediation model is developed and we have completed the dissemination wave, we will assess and measure the magnitude of each pathway with data from participants who complete the adapted Home Care Commission-COMPASS program. While we do not expect that pathways in those latter analyses will be statistically significant, given the small sample size, we will compare effect sizes in each pathway as they relate to path effects in the original cohort.

We will determine the intervention’s economic impact by measuring and computing intervention costs and contrasting them with estimated outcome-related savings. Our survey measures include potential cost saving outcomes, such as self-reported lost work time due to injuries and illnesses, absenteeism, and turnover intentions. We will also collect expanded economic-related data from agencies and organizations that “own” the data for our population of HCWs. We plan to work with the SEIU health care trusts to obtain health care cost data from health care providers for HCWs participating in the study. We will request these expanded workers compensation and health care cost data for participants in both arms of the study retrospectively (36 months prior to enrollment) and prospectively (12 months post-enrollment).

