## Discussion

The COMPASS study is a cluster randomized controlled trial to improve the health and safety of HCWs. Its design is theory-based and structured to meet the needs of these low-wage, isolated workers. Mediation analysis will assist in confirming whether the program impacts purported mediating variables and validates its conceptual underpinnings. The program has several unique components. First, it is held away from the job as, unlike typical employees, HCWs lack a shared worksite. Second is the explicit attention to building a community of practice and providing social support for these lone workers. The scripted, peer-led format has worked in other settings [35, 36], and for HCWs it may further enhance relevance and social support. In addition, having both individual and team level goals operating simultaneously may augment behavior change [31, 32].

We recognized that HCWs have busy home lives, often also providing care for family members, and that they may change consumer-employers during the program, making attendance difficult. Sessions are being held at locations and times to facilitate participation, and strategies are in place to minimize attrition. As with Oregon Home Care Commission classes, HCWs are paid for attending each session, and an escalating reimbursement structure accompanies data collection activities. In formatting manuals and workbooks, we needed a balance between a scripted format to maintain fidelity across groups and enough flexibility to build ownership and allow unscripted interactions that would enhance social support. We will observe all sessions, record adherence to the format, and document any deviations.

The lessons have a balance of safety and health promotion topics. Review of the literature identified only 17 published TWH programs that addressed both safety and health promotion in their intervention and assessment methods, and most lacked a balanced focus [48]. Simultaneously working on health protection and promotion may have advantages. Recent comparison of concurrent versus sequential behavior interventions indicates that addressing behaviors simultaneously is as effective and may be synergistic [88–90].

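### The 6-month mediation model takes mediator and outcome from the same survey, so a significant indirect effect cannot by itself confirm the program's theory

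*Protocol article*

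**What the plan says.** Under Methods, Overview and timeline, both arms are surveyed at months 0, 6 and 12 only. Under Data collection, Quantitative: "The HCW survey includes demographic, work-health history items and a battery of outcome and potential mediating measures". Table 2 lists the primary outcomes and the three purported mediators (community of practice, social support, team cohesion) as constructs of that one survey. On recall, "Behavioral items, unless otherwise noted, are anchored" to the past month. No recall period is stated for the mediator scales.

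The only power figure for mediation, 0.72, is the power "to detect mediated effects at the 6-month time point where both of the paths to and from the purported mediator" have medium size (a = 0.3, b = 0.3). The analysis section describes the wave-one model as "using the pretest measures as predictors of the corresponding post-test outcomes and medicating variables" (the last phrase evidently means mediating variables). It also announces cross-sectional and longitudinal models, the latter as latent growth models. It does not state a model in which the mediator at one visit predicts the outcome at a later visit.

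The abstract says that mediation analysis will confirm the theory. The Discussion says: "Mediation analysis will assist in confirming whether the program impacts purported mediating variables and validates its conceptual underpinnings".

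**The concern.** The section on theoretical basis separates two links. The action theory runs from intervention to mediator, and the conceptual theory runs from mediator to behaviour, with the mediator as the proximal variable. Randomisation protects the first link but not the second. For the second link, the 6-month model has only the association between two parts of one questionnaire completed at one sitting. Mood on the day or a common response style could create that association without any effect of the mediator. The article itself concedes that many measures are self-reported and open to social desirability bias.

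Confirming the theory is a stated purpose of the trial, and the wave-two groups are to be compared, pathway by pathway, with the wave-one model. A mediator-to-outcome path that cannot be interpreted would carry over into that comparison. The primary between-arm comparison is not affected.

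**Working it through.** **Inputs from the article.** Planned n = 160 in 16 groups of 10; ICC 0.02; attrition 25% per testing time point; a = b = 0.3; stated mediation power 0.72. Analysed numbers: 160 × 0.75 = 120 at month 6, and 120 × 0.75 = 90 at month 12 if attrition is cumulative.

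**Assumptions.** The article gives no alpha, sidedness or test for the 0.72, so 5% is assumed. It gives no same-visit residual correlation between mediator and outcome, so a range of 0.1 to 0.3 is shown.

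**1. The plan's own figure.** Design effect 1 + (10 − 1) × 0.02 = 1.18, so effective n = 160/1.18 = 135.6.
- Path a: z = 0.3 × √135.6 / √(1 − 0.09) = 3.66.
- Path b: z = 0.3 × √135.6 × √(1 − 0.09) / √(1 − 0.09) = 3.49.
- Sobel: z = 1/√(1/3.66² + 1/3.49²) = 2.53; two-sided power Φ(2.53 − 1.96) = 0.715.

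A one-sided Sobel test with n = 120 and design effect 1.13 gives 0.723. The 0.72 can thus be reproduced, though only after trying several variants. The figure is not the error.

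**2. What the 6-month test claims when b is zero.** The joint test is positive when both paths are significant. Its rate is about the power for path a times the probability that the mediator-outcome partial correlation r is significant. With n = 120, ignoring clustering:
- Path a: z = 0.3 × √120 / √0.91 = 3.45; power 0.931.
- Mediator-outcome association: z = atanh(r) × √(120 − 4).

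| r (assumed) | z | P(significant) | × 0.931 |
|---|---|---|---|
| 0.1 | 1.08 | 0.191 | 0.18 |
| 0.2 | 2.18 | 0.588 | 0.55 |
| 0.3 | 3.33 | 0.915 | 0.85 |

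Simulation with 2,000 trials per cell gives the same 18%, 55% and 85%. At n = 90 it gives 14%, 39% and 70%; at n = 160, 25%, 69% and 95%. A re-run with 16 clusters, ICC 0.02 and baseline adjustment gives 18%, 55% and 87% at n = 120.

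**3. Real against spurious mediation.** In a separate simulation (3,000 runs, 120 participants in 16 clusters, baseline adjustment), the test was positive in 79% of runs when the mediator truly drove the outcome (a = b = 0.3). It was positive in 80 to 81% when there was no mediator effect but a same-visit residual correlation of 0.3. When the outcome drove the mediator instead, it was positive in 14%.

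**4. What a lagged model would do.** Month-6 mediator to month-12 outcome, adjusted for arm and month-6 outcome, with an assumed outcome stability of 0.5:
- Shared influence confined to the month-6 visit (correlation 0.3, b = 0): positive in 4 to 6%.
- Shared influence that persists to month 12 (b = 0): positive in 54 to 69% at n = 90 to 120.
- True mediation complete by month 6 and only maintained afterwards: positive in 4% (n = 90) and 5% (n = 120), against 71% and 87% for the 6-month test.
- Mediator also acting at month 12: positive in 25% and 33%.

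Generic power for a = b = 0.3 at n = 90 is 0.50 to 0.54 (two-sided Sobel, with and without design effect) or 0.63 to 0.69 (joint significance).

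**The case against.** The strongest reply is that the article already plans longitudinal mediation models. The choice of lag, and of the model that carries the claim, is detail that a condensed article may leave to the analysis plan. This stands in part: a reader might infer that the trial cannot test its theory at all, and that would be wrong, because the visits at months 6 and 12 permit a lagged model. But the shared survey, the three visits and the 6-month power statement are fixed here, and no analysis plan can create an earlier post-randomisation mediator for the 6-month test.

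A reader might also infer from the past-month recall that the outcome precedes the mediator. The documents do not support this. The window is a default for behavioural items, the mediator scales have no stated window, and cohesion reported at month 6 may reflect bonds formed well before the last month. Concurrent is as far as the text goes.

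It can fairly be said that the Discussion sentence speaks first of the program's effect on mediators, which month-6 data test properly. The sentence goes on to the conceptual underpinnings, however, and in the article's own terms these are the mediator-to-behaviour link.

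The rates do depend on assumed correlations, and only the shared-influence scenario gives large ones. Reversed causation gave 14%, above 5% but modest.

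Finally, it is tempting to make the lagged model the main one. The results in step 4 speak against that.

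**Conclusion.** The point holds in a limited form. At month 6 the intervention-to-mediator path is randomised and testable, while the mediator-to-outcome path is a concurrent association. A significant 6-month indirect effect cannot by itself separate mediation from a shared same-visit influence. At n = 120 with a = 0.3 and b = 0, the false-claim rate is about 18%, 55% and 85% for assumed residual correlations of 0.1, 0.2 and 0.3. Even the lowest is more than three times a nominal 5%.

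This does not show that the 0.72 is miscalculated, that the theory is wrong or untestable, or that a lagged analysis would settle it. The lagged model adjusted for the month-6 outcome asks whether the mediator drives further change after month 6. It misses mediation already complete by then and does not remove persistent confounding.

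**What to change.** - Keep the 6-month model, but describe its mediator-to-outcome path as a concurrent association, and the 0.72 as power to detect an indirect effect that includes such a path.
- Add as a supporting analysis the month-6 mediator to month-12 outcome model, with and without adjustment for the month-6 outcome, and state its power.
- Add a sensitivity analysis for unmeasured mediator-outcome confounding.
- In the abstract and Discussion, limit the claims of confirming and validating to the randomised intervention-to-mediator path. Call a mediated effect consistent with the theory only where the 6-month, lagged and sensitivity results agree.

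The cost is a little more analysis and a weaker claim; no visit or measure is added. The lagged model's power is about 0.50 to 0.69 at n = 90 for a = b = 0.3. For this reason, and because of the limits shown in step 4, it should neither replace the 6-month model nor decide the theory claim alone.

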### Data analysis

#### Quantitative

In general analyses we will use SPSS (SPSS, Chicago, IL, USA) and M-Plus (Muthén and Muthén, Los Angeles, California, USA) for structural equation modeling. Survey instrument assessment will begin by confirming predicted item constructs, augmented with exploratory factor analysis, to establish reliable summary scales with maximum internal consistency.

Our primary hypothesis is that the intervention will be more effective than a usual treatment control condition for increasing safety and health behaviors. To test these hypotheses, we will evaluate between-group differences using an intent-to-treat approach and generalized estimating equations with participants nested in groups. We will begin by computing interaction contrasts on pre/post-intervention differences across groups. Intervention group membership will be the between-subjects factor, and pre/post-intervention assessment scores on primary outcomes will be the within-subjects factor. The interaction contrast approach will allow efficiently comparing the two groups on each dependent measure with a focused one degree of freedom hypothesis test; similar analyses will be repeated for the follow-up assessment time point.

We will also test for group differences in secondary outcomes, such as injuries and health measures. Discrete-scaled and rare secondary outcomes (for example, injuries) will be analyzed with Poisson or zero-inflated Poisson regression models. In models for discrete-scaled outcomes, we will use baseline values as a pre-treatment covariate to account for existing individual differences and boost statistical power to detect intervention effects.

Using mediation analysis to deconstruct the action and conceptual theory components has been a feature of our programs [79–81]. For continuous outcomes, structural equation modeling will be used to evaluate relations among variables using model-fit indices. For binary or ordinal outcomes, each mediator’s contribution to predicting group states for outcomes will be conducted using logistic regression analysis. Cross-sectional and longitudinal models will be developed to identify the strength of the relation of purported model constructs to outcome variables, and model-fit indices calculated. The multilevel capabilities of latent growth modeling make possible construction, estimation, and testing of a variety of complex models utilizing hierarchically structured data, such as ours. Each potential mediating variable will be evaluated in separate models, followed by multiple mediator models. Longitudinal mediation effects will be assessed in the latent growth modeling framework. These methods also allow for identification of subgroups for which the program has a differential effect. Variables coding these subgroups are moderator variables, and they usually are equivalent to interaction effects. Models with mediators and moderators allow simultaneous assessment of how a program works (mediation) and whether or not the program works differentially for certain participants (moderation). For example, a common result in prevention research is that effects vary according to pre-existing risk. This type of mediation modeling can provide information about subgroups experiencing large effects and others for which it is ineffective or even counter-productive.

For the initial randomized control trial wave, all participant data will be used, and group assignment will be represented by a dummy code variable (that is, intervention = 1, control = 0), using the pretest measures as predictors of the corresponding post-test outcomes and medicating variables, with the dummy code variable accounting for group differences at baseline. Once that mediation model is developed and we have completed the dissemination wave, we will assess and measure the magnitude of each pathway with data from participants who complete the adapted Home Care Commission-COMPASS program. While we do not expect that pathways in those latter analyses will be statistically significant, given the small sample size, we will compare effect sizes in each pathway as they relate to path effects in the original cohort.

We will determine the intervention’s economic impact by measuring and computing intervention costs and contrasting them with estimated outcome-related savings. Our survey measures include potential cost saving outcomes, such as self-reported lost work time due to injuries and illnesses, absenteeism, and turnover intentions. We will also collect expanded economic-related data from agencies and organizations that “own” the data for our population of HCWs. We plan to work with the SEIU health care trusts to obtain health care cost data from health care providers for HCWs participating in the study. We will request these expanded workers compensation and health care cost data for participants in both arms of the study retrospectively (36 months prior to enrollment) and prospectively (12 months post-enrollment).

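### The primary test is a difference-in-change contrast, which is less precise than adjusting for the baseline already collected; with complete data the loss is (1 − r)/2, and the article gives no r

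*Protocol article*

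**What the plan says.** All of this is in the protocol article, Data analysis, Quantitative.

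- The primary hypothesis is tested by intention to treat with "generalized estimating equations with participants nested in groups".
- The first and only primary model described is this: "We will begin by computing interaction contrasts on pre/post-intervention differences across groups". Its structure is then fixed: "Intervention group membership will be the between-subjects factor, and pre/post-intervention assessment scores on primary outcomes will be the within-subjects factor". The same analysis is repeated at the follow-up time point.
- The reason given is efficiency: "The interaction contrast approach will allow efficiently comparing the two groups on each dependent measure with a focused one degree of freedom hypothesis test".
- For discrete-scaled outcomes, in the paragraph on secondary outcomes, baseline has a different role: "we will use baseline values as a pre-treatment covariate to account for existing individual differences and boost statistical power to detect intervention effects".
- The wave-one mediation model also conditions on baseline, "using the pretest measures as predictors of the corresponding post-test outcomes".

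In the primary model, then, the baseline score is one level of the outcome. In two other parts of the plan it is a covariate.

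**The concern.** In a randomised trial both approaches estimate the same programme effect for a continuous outcome, so the choice between them is one of precision. A change score subtracts the whole baseline value. A covariate-adjusted model subtracts only the part that predicts the follow-up score. When r is below 1, subtracting all of it adds noise, and when r is below 0.5 it adds more noise than it removes.

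The text recommends the contrast as efficient, yet a more precise analysis of the same data is available and is used elsewhere in the plan with power as a stated reason. What is at stake is the precision of every primary comparison in a trial of 160 participants, whose Power and sample size section puts power for 12-month maintenance at only 0.74.

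**Working it through.** **Inputs from the article.** 160 participants, 80 per condition, in 8 groups of 10 per condition; intraclass correlation 0.02; power 0.85 at 6 months and 0.74 at 12 months (Power and sample size). Attrition of 25% for each testing time point (Participants section). Not given: effect size as a number, standard deviation, alpha, sidedness, and r.

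**The plan's own figures.** Power of 0.85 cannot be derived forward without an effect size. Working backwards with a two-sided 5% test (assumed) and 25% lost by 6 months:
- Remaining per arm: 80 × 0.75 = 60. Mean group size 7.5. Design effect 1 + 6.5 × 0.02 = 1.13.
- Standardised difference for power 0.85: 2.996 × √(2 × 1.13/60) ≈ 0.58.
- A further 25% lost by 12 months: 60 × 0.75 = 45 per arm, mean group size 5.625, design effect 1.0925. Power for 0.58 is about 0.75, against the stated 0.74.

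The two figures fit together, but they do not reveal whether the variance behind them was that of a change score, a follow-up score or an adjusted score.

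**Is the planned contrast a change-score analysis?** On complete simulated data the group-by-time coefficient from the estimating equations and the simple difference in mean change were both 0.3505. It is.

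**Complete-data comparison.** Per person, in units of the outcome variance and with equal variance at both times:
- follow-up score alone: 1
- change score: 2(1 − r)
- baseline as covariate: 1 − r²
- ratio, adjusted to change: (1 − r²)/[2(1 − r)] = (1 + r)/2
- share of precision lost by the change score: 1 − (1 + r)/2 = (1 − r)/2

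| assumed r | change | adjusted | loss | participants an adjusted analysis needs to match 160 on change |
|---|---|---|---|---|
| 0.3 | 1.40 | 0.91 | 35% | 104 |
| 0.5 | 1.00 | 0.75 | 25% | 120 |
| 0.7 | 0.60 | 0.51 | 15% | 136 |
| 0.8 | 0.40 | 0.36 | 10% | 144 |

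The ratio is below 1 for every r below 1. The change score exceeds 1, and so is worse than ignoring baseline, when r is below 0.5.

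**Clustering.** In 20,000 simulated trials per setting (16 groups of 10, intraclass correlation 0.02) the loss at r = 0.3, 0.5 and 0.7 was 33%, 24% and 14% when group effects correlated over time as strongly as individual scores. It was 36%, 29% and 19% when group effects were uncorrelated over time. Clustering does not change the picture.

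**Attrition.** Suppose the estimating equations keep all n = 80 baseline scores per arm and model the within-person correlation, with c participants followed up. Ignoring clustering, the per-arm variance is then
- contrast: (1 − r²)/c + (1 − r)²/n
- adjusted: (1 − r²)/c

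At r = 0.5:
- 6 months, c = 60: 0.75/60 = 0.01250 and 0.25/80 = 0.003125. Loss = 0.003125/0.015625 = 20%.
- 12 months, c = 45: 0.75/45 = 0.01667. Loss = 0.003125/0.01979 = 16%.

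At r = 0.7 the same formula gives 12% and 9%. Setting c = n returns 2(1 − r)/n, the complete-data result.

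**The case against.** The strongest reply is that the contrast is a valid, unbiased and widely used analysis, so this is a choice between two sound estimators. That stands: nothing here is a bias or a validity error.

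The word on efficiency can also be read as praise for a single focused test, with no claim of superiority over baseline adjustment. That is a fair reading, but the condition coefficient in a baseline-adjusted model is also a one-degree-of-freedom test, so the stated advantage gives no reason to prefer the contrast.

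It may be said that the text only begins with these contrasts and that a fuller analysis plan may exist. No other primary model is described in the article, so the contrast is what it fixes.

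Four stronger readings are tempting and should be resisted.

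- **That a quarter of the precision is lost.** This needs r = 0.5 and complete data. No r is stated, and it may differ by outcome and time point.
- **That the stated powers are wrong, or would rise by a known amount.** At r = 0.5 (two-sided 5%), if 0.85 and 0.74 refer to the change contrast, adjustment gives 0.93 and 0.85. If they already assume adjustment, the contrast delivers 0.74 and 0.62. If they refer to follow-up scores alone, the contrast meets them exactly at r = 0.5 and exceeds them above it. The article does not say which applies.
- **That only the primary comparison lacks baseline adjustment, so that the plan contradicts itself.** The covariate is stated for discrete-scaled outcomes; continuous secondary health measures have none stated either. Handling counts and rare events with a different model is not a contradiction.
- **That the primary and mediation analyses will disagree.** For continuous outcomes they target the same effect under randomisation and differ only through chance baseline imbalance. They need not agree in a given data set, but they are not inconsistent in aim.

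**Conclusion.** The point holds as an avoidable loss of efficiency on the primary outcomes. Its direction does not depend on any assumption beyond randomisation, similar outcome variance at both times, and r below 1. Its size does: 35% to 10% of precision for assumed r from 0.3 to 0.8 with complete data. It is smaller (20% at 6 months and 16% at 12 months for r = 0.5) if the fitted model retains all baselines and the within-person correlation, with attrition of 25% compounding at each visit. The article does not state the working correlation, so which of these cases applies is open. Neither the validity of the contrast nor the stated powers are called into question.

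**What to change.** For each primary outcome, define the primary analysis as a generalised estimating equation model of the 6- and 12-month scores on condition, with the baseline score as covariate and group as the clustering unit. A repeated-measures model with a common baseline mean across arms is an equivalent choice, and it uses every baseline score. Keep the interaction contrast as a named sensitivity analysis.

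The cost is a change of wording. Baseline scores are already collected at month 0. Participants learned their condition only after baseline data collection, so baseline is a legitimate covariate. The Trial status section reports that no baseline analyses have occurred. The change should be recorded before outcomes are examined by condition.
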